### Data Analysis Plan

Feasibility outcomes (research question 1; recruitment, retention, adherence, and satisfaction rates) will be analyzed using descriptive statistics (mean [SD] or frequency [%]), as appropriate. Preliminary estimates of effects *(*research question 2*)* will be reported using mean (SDs) and CIs of outcomes for continuous outcomes. Given the pilot nature of this trial and the limited sample size, Cohen *d* effect sizes will be calculated and reported for each secondary outcome. Effect sizes will be interpreted alongside CIs to provide estimates of the magnitude of effect and to inform a future full-scale trial. Medication use will be summarized descriptively for each treatment group. The proportion of participants using each medication class will be reporting using frequencies (%s), while duration of medication use and dosage will be summarized using mean (SDs) or median (IQRs), as appropriate. The frequency and nature of adverse events (research question 3) will be summarized descriptively. An intention-to-treat analysis will be conducted, with missing data handled using multiple imputation. STATA/MP (version 14; StrataCorp) will be used for all statistical analyses, with significance set at *P*<.05.

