### Sample Size

Based on sample size calculations for pilot data [22,23], we expect to recruit 30 participants for the study (15 in each group). For this project, the sample size was calculated based on the expected proportion of success of the primary feasibility outcome [23]. Using a Z value corresponding to a 95% CI (1.96), a desired margin of error (E) of 0.2, and an estimated population proportion of success (p) of 0.75 (based on expected estimated adherence rates), the calculated sample size for this pilot study was 18 participants (9 per group). With an expected dropout rate of up to 30% [24], the final sample size for this project was set at 30 participants (15 per group) to accommodate 1:1 block randomization and provide a conservative buffer.

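### Cohen d, planned with no small-sample correction, is biased upward by about 3% on average (at most about 4%) in this pilot; Hedges g would remove the bias at no cost

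*Protocol article*

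**What the plan says.** The Data Analysis Plan, giving the pilot nature and small size of the trial as its reason, states that "Cohen *d* effect sizes will be calculated and reported for each secondary outcome". Their purpose follows: "Effect sizes will be interpreted alongside CIs to provide estimates of the magnitude of effect and to inform a future full-scale trial". The Abstract (Methods) repeats the choice of Cohen d and the same purpose. Neither place mentions a small-sample correction, and neither rules one out.

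On size, the Sample Size section says "we expect to recruit 30 participants for the study (15 in each group"), after a precision calculation that gave 18, and allows for dropout of up to 30%. The Data Analysis Plan also reports means, SDs and CIs for continuous outcomes, summarises medication use descriptively, and plans an intention-to-treat analysis with multiple imputation.

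**The concern.** Cohen d divides a difference in means by a pooled SD estimated from the same few patients. The reciprocal of an SD estimated on few degrees of freedom is too large on average, so d is too large on average by a known factor that depends only on the degrees of freedom. The bias has the same direction for every continuous outcome and is separate from chance. The article's reason for using d, the limited sample size, is also the condition under which the correction matters.

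What is at stake is the stated use. The size of a two-group trial varies with 1/d², so an effect size that is too large on average points to a later trial that is somewhat too small, if it is used for sizing.

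**Working it through.** **Inputs from the protocol article.** 30 participants, 15 per group, and dropout of up to 30% (Sample Size); Cohen d as the statistic, and multiple imputation (Data Analysis Plan).

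**Assumptions not in the article.** d is the between-group difference over the pooled SD of normal data, so df = N − 2. For the illustration of a later trial: two-sided 0.05, 80% power, true standardised difference 0.5.

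**The plan's own figure.** Z²p(1 − p)/E² = 1.96² × 0.75 × 0.25 / 0.2² = 18.01, which agrees with the stated 18 (19 if strictly rounded up). Allowing for dropout, 18/0.7 = 25.7, so 26 (19/0.7 = 27.1, so 28). The article then sets 30 and describes it as including a buffer. The sample size therefore reproduces, and 30 can be used for the degrees of freedom.

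**Degrees of freedom.**
- All 30 analysed: df = 28.
- Complete-case bound: 30 × 0.7 = 21 analysed, df = 19.
- With multiple imputation at the maximum planned dropout, the effective df lies between about 19 and 28.

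**Bias.** The expected value of d is the true value divided by J(df), where J(df) = Γ(df/2) / [√(df/2) Γ((df − 1)/2)], approximately 1 − 3/(4df − 1). The mean bias is 1/J − 1. If the mean of d were put into a 1/d² formula, the shortfall in size would be 1 − J².

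| Analysed | df | J | Mean bias | Shortfall if sized on mean d |
|---|---|---|---|---|
| 30 | 28 | 0.9729 | +2.8% | 5.3% |
| 21 | 19 | 0.9599 | +4.2% | 7.9% |

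**Illustration at true d = 0.5.** The normal-approximation size per arm is 2 × (1.96 + 0.8416)² / 0.5² = 62.8, so 63. With the mean of d in its place:
- 0.5/0.9729 = 0.514 gives 60 per arm, with true power about 78%.
- 0.5/0.9599 = 0.521 gives 58 per arm, with true power about 77%.

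**Bias against sampling error at true d = 0.5** (one million simulated pilots per case; means and SDs agree with the noncentral t distribution).

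| Analysed | SD of d | Central 95% range of d | Share of pilots with d above 0.5 | RMSE of d | RMSE of g |
|---|---|---|---|---|---|
| 30 | 0.39 | −0.22 to 1.30 | 50.5% | 0.386 | 0.375 |
| 21 | 0.47 | −0.37 to 1.49 | 50.5% | 0.471 | 0.451 |

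The bias is 0.014 with 30 analysed and 0.021 with 21, about 4% of one SD of d in each case (0.014/0.39 = 3.6%; 0.021/0.47 = 4.5%).

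**The case against.** A reader might infer that every secondary effect will be overstated by 3 to 4%, or that the next trial is bound to be underpowered. Neither follows. The bias belongs to the mean over repeated trials, and any one estimate falls below the true value almost as often as above it.

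A reader might also take d as the figure on which the full trial will be sized. The article says only that d, read with its CI, will inform that trial. Means and SDs are reported too, progression rests on feasibility (Primary Outcome section and Table 2), and Strengths and Limitations calls the secondary results preliminary. The 5 to 8% shortfall is therefore conditional on a step the article does not take. The larger figure is also a bound: 21 analysed is a complete-case count at the maximum dropout, whereas the plan is intention-to-treat with imputation.

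Two further objections carry less weight. The first is that the choice between d and g is a detail for the analysis plan. Whether a correction will be applied may be settled there, but the article does name the statistic, its reason and its purpose, so a comment on that choice is fair. The second concerns the median. At true d = 0.5 the median d is about 0.505 (df 28) or 0.507 (df 19), so the median implied size is only about 1.8% or 2.6% too small, whereas with g it is about 3.8% or 5.7% too large. That is correct: g does not improve the typical implied size. It does remove the mean bias and lower the RMSE, and in simulation of later trials sized on the estimate it raises average true power by about 1 to 2 percentage points, so the objection does not defeat the change.

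**Conclusion.** The point holds as a minor improvement, not as an error that threatens the trial. As named, without a correction, Cohen d is biased upward on average by about 2.8% with all 30 analysed and by at most about 4.2% at the planned maximum dropout. A consequence for a later trial (about 5%, up to 8%, too small) arises only if that trial is sized on the mean of d. The percentages rest on a between-group d with a pooled SD and normal data; the power figures also rest on the assumed true effect, significance level and power.

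The imprecision of a pilot effect size is far more important than this bias, and the correction does not address it. No feasibility result or progression decision is affected.

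**What to change.** In the Abstract and the Data Analysis Plan, replace Cohen d with Hedges g, that is d × J(df), with its 95% CI for each continuous secondary outcome; or state that d will carry this small-sample correction. Keep the planned raw means, SDs and CIs, and leave medication use descriptive.

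The cost is one multiplication per outcome and no new data. The only downside is slightly smaller reported effects. The article reports 3 participants recruited and schedules analysis for June and July 2027, so the change can be made well before any analysis.

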## Introduction

### Background

Melanoma, a serious form of skin cancer, has become increasingly prevalent in Canada [1]. In recent years, Canadians have become increasingly aware of the importance of early detection and treatment [1]. However, surgical intervention for melanoma, while often necessary for effective management, can result in significant physical and emotional challenges for patients [2,3]. In Canada, the treatment landscape for melanoma is evolving with the introduction of new neoadjuvant immunotherapy regimens aimed at improving patient outcomes for those with more advanced melanoma [4,5]. Recent advancements include the use of combination therapies that integrate immune checkpoint inhibitors with targeted therapies, which are designed to enhance tumor response before surgical resection [4]. These innovative approaches aim to reduce tumor size and potentially improve the rate of complete surgical removal [4]. Ongoing clinical trials continue to evaluate the effectiveness and safety of these regimens, reflecting a commitment to optimizing preoperative treatment strategies and improving outcomes for those with melanoma [6]. Neoadjuvant immunotherapy is commonly administered over 6 weeks after the initial consultation for ipilimumab-nivolumab combination therapy or over 12 weeks after the initial consultation for pembrolizumab monotherapy. While these advances offer promising improvements in disease management, the introduction of immunotherapy during the preoperative period may also increase treatment burden. Patients may experience the combined effects of surgery and immunotherapy-related toxicities, including fatigue, reduced muscle strength, and impaired physical function. These potential consequences should be considered and proactively addressed alongside these changes in medical management.

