## Methods

### Study Design

This is a pilot, parallel group randomized controlled trial (RCT). It will use a 1:1 allocation ratio, and participants will be randomly assigned to either the intervention or control group. Outcome assessments will be conducted at baseline and postintervention time points with assessors and data analysts blinded to group allocation. The protocol adheres to the SPIRIT (Standard Protocol Items: Recommendations for Interventional Trials) 2025 checklist [21] for protocols of randomized trials. Figure 1 shows the flow of participants across the study and associated analysis time points.

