#### Intervention Group

The intervention group (CARE intervention) will include 4 perioperative intervention sessions led by a physiotherapist or kinesiologist trained in the treatment of individuals with cancer. The total intervention time will be approximately 4 months, with 2 of the intervention sessions occurring prior to surgery and 2 occurring after surgery. The intervention was designed to coincide with the immunotherapy treatment regime and key perioperative milestones [20]. The 2 preoperative sessions provide an opportunity for assessment, exercise education, prehabilitation, and development or an individualized exercise plan. They will be conducted in person whenever participants visit the cancer center for a scheduled appointment. The postoperative sessions support reassessment, progression of rehabilitation, management or postsurgical issues, and transition to long-term self-management. Participants will have the option of taking part in the postsurgery sessions in person or virtually. The approximately 4-month duration was selected to encompass the presurgical and early postsurgical recovery period while maintaining feasibility and minimizing participant burden in this pilot trial.

Each intervention session will include five components based on our previous research and guidelines for survivors of cancer: (1) review of current symptoms and function, (2) educational modules on exercise viewed on an iPad with the trainer, (3) tailored rehabilitation to maximize function, (4) home exercise program development or review, and (5) action plan development for participants to work on between sessions. Table 1 describes each intervention component. Figure 2 provides an overview of the CARE intervention components across the study period.

**Table 1 table1:** Components of the CARE intervention.

Component	Description
Review of current symptoms and function	Sessions 1-4 (items checked) Current symptoms (eg, pain, fatigue, range of motion, strength, balance scan) Posture Functional concerns (mobility observation) Vital signs (eg, heart rate, blood pressure, SpO2) Other changes since last visit

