#### Medication Use

Medication use will be collected using a self-report questionnaire. The questionnaire will ask participants to list the medications they are currently using and have used 7 days prior to the assessment (drug name and dosage). After the surgery, the questionnaire will also ask if they have taken specific medication since surgery (acetaminophen, antiinflammatories, muscle relaxants, neuropathic pain medications, or narcotics), how long they took the medication after the surgery, and the dosage. Tracking medication will allow us to identify changes in medications that may occur during the perioperative period, explore whether medication use acts as a potential confounder when interpreting intervention-related change, and inform the design and covariate selection for a future larger-scale trial.

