### End Points

The intervention will take place over 4 months, with assessments taking place before and after the intervention. Therefore, all data are expected to be collected within 9 months. Data analysis will then be conducted and is expected to take approximately 1 month.

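### Duration of postoperative medication use is summarised by a plain mean or median of the time reported at one follow-up visit, although for continuing users that time is only a lower bound

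*Protocol article*

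**What the plan says.** All references are to the protocol article.

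- **Timing.** Study Design: "Outcome assessments will be conducted at baseline and postintervention time points". End Points: "The intervention will take place over 4 months, with assessments taking place before and after the intervention". One scheduled outcome assessment therefore follows surgery.
- **Measurement.** Under Medication Use, the postoperative questionnaire asks whether five classes ("acetaminophen, antiinflammatories, muscle relaxants, neuropathic pain medications, or narcotics") were taken since surgery, and "how long they took the medication after the surgery, and the dosage". The same questionnaire has participants "list the medications they are currently using and have used 7 days prior to the assessment (drug name and dosage".
- **Analysis.** The Data Analysis Plan gives frequencies by class, "while duration of medication use and dosage will be summarized using mean (SDs) or median (IQRs), as appropriate". It also promises Cohen d for every secondary outcome, and multiple imputation for missing data.
- **Role.** Medication use is a secondary outcome. Research Questions and Hypotheses expects it to be better with the intervention than with usual care.
- **Calendar.** Intervention Group: "The total intervention time will be approximately 4 months, with 2 of the intervention sessions occurring prior to surgery and 2 occurring after surgery". Background: "Neoadjuvant immunotherapy is commonly administered over 6 weeks after the initial consultation for ipilimumab-nivolumab combination therapy or over 12 weeks" for pembrolizumab monotherapy.

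The article does not give the interval from surgery to the follow-up visit or any expected duration of use. It does not say how a duration that is still running enters the summary.

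**The concern.** How long a drug was taken can be known at a visit only for people who have stopped. Someone still taking it can report the time so far, which is a lower bound. The article names an estimator for these values, and that estimator treats every value as complete. The choice offered between mean and median concerns the shape of the distribution and not unfinished durations. Multiple imputation is planned for missing values, and a lower bound is not described as missing.

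The cap on each value is that participant's time from surgery to the visit. If the visit is tied to a programme of fixed length and the preoperative part lasts 6 or 12 weeks, the cap depends on the regimen. The plain mean then describes use up to a day that varies between participants. At stake is what the pilot passes on about medication use. Medication Use says these data should inform the design and covariate selection of a larger trial, and the Data Analysis Plan says effect sizes should inform that trial.

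**Working it through.** The article states no figure for medication duration, so there is none to reproduce. What follows is a conditional calculation.

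**1. What the plain mean estimates.** Let T be the time from surgery to stopping and W the time from surgery to the visit. The reported value is min(T, W), so the mean estimates E[min(T, W)] and not E[T].

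**2. Windows (assumed).** Four months = 4 × 30.4375 / 7 = 17.4 weeks. Suppose the 4 months start with immunotherapy, surgery follows directly at its end, and the visit falls at the end of the 4 months. Then W = 17.4 − 6 = 11.4 weeks or 17.4 − 12 = 5.4 weeks. The 4, 6 and 12 are in the article; the alignment is not.

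**3. Durations (assumed).** T is exponential with mean m, and one arm's mean is twice the other's. Then E[min(T, W)] = m(1 − exp(−W/m)), the proportion still taking the drug at the visit is exp(−W/m), and the true median is m·ln 2. For example, with m = 8 and W = 5.4: 8 × (1 − exp(−0.675)) = 3.93 weeks, with exp(−0.675) = 51% still taking the drug.

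| True means (weeks) | W | Reported means | Reported difference | Share kept | Still taking |
|---|---|---|---|---|---|
| 1 v 2 | 5.4 | 1.00 v 1.87 | 0.87 of 1 | 87% | 0% v 7% |
| 1 v 2 | 11.4 | 1.00 v 1.99 | 0.99 of 1 | 99% | 0% v 0% |
| 2 v 4 | 5.4 | 1.87 v 2.96 | 1.10 of 2 | 55% | 7% v 26% |
| 2 v 4 | 11.4 | 1.99 v 3.77 | 1.78 of 2 | 89% | 0% v 6% |
| 4 v 8 | 5.4 | 2.96 v 3.93 | 0.96 of 4 | 24% | 26% v 51% |
| 4 v 8 | 11.4 | 3.77 v 6.08 | 2.31 of 4 | 58% | 6% v 24% |
| 8 v 16 | 5.4 | 3.93 v 4.58 | 0.66 of 8 | 8% | 51% v 71% |
| 8 v 16 | 11.4 | 6.08 v 8.15 | 2.08 of 8 | 26% | 24% v 49% |

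Differences are taken from unrounded means.

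**4. Medians.** With one common window, a median is unchanged while fewer than half of the arm are still using. At 11.4 weeks the difference in medians is unchanged in all four cases. At 5.4 weeks it is unchanged for 1 v 2 and 2 v 4, becomes 2.63 instead of 2.77 for 4 v 8, and 0 instead of 5.55 for 8 v 16. If windows are mixed within an arm, the shorter one must also lie beyond the median.

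**5. Cohen d.** By simulation (one million per arm), d without truncation is 0.63. In the order of the table it is 0.66, 0.62, 0.51 and 0.39 at 5.4 weeks, and 0.64, 0.66, 0.63 and 0.52 at 11.4 weeks.

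**6. Direction is not fixed.**
- Unequal windows: equal true use in both arms (mean 8 weeks), with 60% v 40% of participants in the longer window. The difference is (0.60 − 0.40) × (6.08 − 3.93) = 0.43 weeks where none exists.
- Crossing curves: one arm all stop at 5 weeks; in the other, 70% stop at 2 weeks and 30% at 12. True means are 5 and 0.7 × 2 + 0.3 × 12 = 5, so the difference is 0. With W = 5.4 the second mean becomes 0.7 × 2 + 0.3 × 5.4 = 3.02, and a difference of 1.98 weeks appears.

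**The case against.** A reader might infer that the plan counts continuing users as having stopped on the visit day. It does not say so. It gives no coding rule, and coding may sit in the questionnaire, the full protocol or an analysis plan that is not shown. The list of current medications in the same questionnaire should also let most continuing users be identified. Both points stand. They do not remove the concern, because the article does fix the summary of duration, and that summary makes no use of the current-use information.

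A reader might also infer that any difference between arms must shrink. Steps 3 to 6 do not support this. With short use almost all of the mean difference survives, the median is often untouched, Cohen d can stay level or rise slightly, and unequal windows or crossing curves can create a difference.

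A third objection is that a mean restricted to a common day does not recover the lost difference. That is correct: at 5.4 weeks it gives the same 0.96 for 4 v 8 weeks. Its gain is a defined quantity with the same limit for everyone. Kaplan-Meier curves for five classes with at most 15 per arm, and fewer users, will also be imprecise.

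Finally, medication use is reported descriptively, Strengths and Limitations calls secondary results preliminary, and progression in Table 2 rests on feasibility criteria alone. That sets the weight of the point.

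**Conclusion.** The concern holds in a limited form and is minor. The stated mean or median treats lower bounds as complete durations. The plain mean therefore estimates use up to a visit day that may vary by regimen. The distortion is most often toward a smaller difference when use is long, and it is negligible when use is short.

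No single percentage can be given as the bias. The share of the mean difference kept runs from 87% to 99% for true means of 1 v 2 weeks to 24% to 58% for 4 v 8 weeks. These ranges depend on exponential durations, on the assumed windows of 5.4 and 11.4 weeks, and on every continuing user reporting the time so far. None of these is stated in the article.

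**What to change.** - **Medication Use.** Use the current-medication list to flag continuing use for each listed class, and add a stop date or a still-taking option to the duration question.
- **Data Analysis Plan.** Report the number still using at the visit by arm and class. Replace the plain mean or median of duration with a Kaplan-Meier summary from surgery among users, censoring continuing users at the visit. State that the median is not reached where half or more are still using.
- **If a mean is wanted.** Report mean days of use up to one common postoperative day, and label it so. State whether non-users are left out or counted as zero, since these are different quantities.

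The cost is one item per class on an existing form and two or three sentences in the plan. The Results section reports 3 participants recruited, so little data would predate the change. The downsides are imprecise estimates with at most 15 per arm, and a restricted mean that describes use only up to the common day. Kaplan-Meier also assumes that visit timing is unrelated to stopping, so the surgery-to-visit interval should be reported by arm.
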